#### Goal intention

The strength of goal intention is assessed with a single item: “How strong is your intention to exercise regularly within the following weeks and months?” Participants can respond on a 6-point Likert scale ranging from 0 = I do not intent to exercise regularly to 5 = I do have a strong intention to exercise regularly.

#### Self-concordance

Self-concordance is measured using the German SSK scale (Sport-und bewegungsbezogene Selbstkonkordanz) [57], consisting of 12 items based on the self-concordance model of Sheldon and Elliot [45]. The SSK scale involves four subscales that measure the intrinsic, identified, introjected, and extrinsic motivation for being physically active. Only participants who indicated having at least a weak exercise-related goal intention (strength of goal intention > 1) are receiving this questionnaire. The 4-point Likert scale ranges from 1 = not true to 4 = true.

This instrument has proved to be a reliable and valid measure of exercise-related self-concordance [58]. In two separate studies reported by Seelig and Fuchs [58], the reliability of the subscales ranged from α = 0.70 (identified motivation) to α = 0.82 (intrinsic motivation). Evidence of validity was provided by a correlation of *r* = 0.47 between the SSK scale and the intention to engage in physical exercise [58].

#### Barriers and barrier management

The two scales of sport-related situational barriers and sport-related barrier management [59] allow detailed analyses of the process of volitional action control in the field of sport and physical activity. The questionnaire to assess perceived barriers contains 13 items presenting the most common sport-related situational barriers. Participants are asked how often these barriers discourage them from engaging in sport activity. The questionnaire assessing strategies for barrier management contains 15 items assessing the most common barrier management strategies. In this questionnaire, participants are asked how often they use these strategies. In both questionnaires, participants rate the items on a 4-point Likert scale ranging from 1 = almost never to 4 = almost always. Both scales are reliable (sport-related barrier management: α = 0.78, situational barriers: α = 0.81) and valid instruments [59].

#### Consequence experience

Expectation about sport-related consequence experience is assessed using an instrument developed and validated by Fuchs [60]. It includes 16 positive and negative versions of outcome experience of physical exercise. Participants are asked to respond on a 4-point Likert scale ranging from 1 = not true to 4 = true. The positive and negative experience items are summed separately. The difference of positive–negative items is derived to provide an outcome experience index [60].

#### Action planning

Participants are asked whether they already know which physical exercise to perform in the following weeks and months. If the answer is “yes,” patients will be asked to note this activity. An opportunity is provided to name a second activity. For each of these activities, participants are asked whether they already know (1) when and (2) where they will perform it, (3) how they will get there, and (4) how often and (5) with whom they will perform the activity. An action planning score is formed by summing the number of positive answers (including naming the activity plus planning details).

#### Pain intensity

We are using an 11-point numerical rating scales for rating the worst, least, and average pain during the last week as well as the current pain level, and the mean of the four scales is calculated. The participants evaluate their pain from 0 to 10, with 0 meaning “no pain” and 10 meaning “pain as bad as you can imagine.” Dworkin and colleagues reported the internal consistency of a composite pain score averaging ratings of current pain, average pain, and worst pain as satisfactory to high (α = 0.77). The composite score was normally distributed, contrary to the individual ratings [61].

#### Pain interference

The Brief Pain Inventory (BPI) allows participants to rate the degree to which their pain interferes with common aspects of emotional and physical function [62, 63]. The seven BPI interference items assess pain interference during the past 24 h on an 11-point scale from 0 (“does not interfere”) to 10 (“completely interferes”). The BPI is a reliable (α = 0.88) and valid measure of the interference of pain with physical and emotional functioning [64].

#### Depression

The eight-item Patient Health Questionnaire depression scale [65] is a valid diagnostic measure of the severity of depressive symptoms based on the *Diagnostic and Statistical Manual of Mental Disorders, Fifth Edition* (DSM-5). With the exception of the symptom of suicidal ideation or self-injurious thoughts, each of the nine DSM-5 criteria for major depression can be scored from 0 (“not at all”) to 3 (“nearly every day”) in the past 2 weeks. The instruments shows satisfactory validity and reliability [66].

#### Anxiety

The seven-item Generalized Anxiety Disorder scale [67] describes the most prominent diagnostic features of the DSM-5 criteria A, B, and C for generalized anxiety disorder. These can be scored from 0 (“not at all”) to 3 (“more than half the days”) during the last 2 weeks. Its reliability and validity is good [65] with excellent internal consistency (α = 0.92) and good test–retest reliability (intraclass correlation coefficient, 0.83).

#### Intervention adherence

The attrition rate (percentage of individuals who no longer use the app, as assessed by their log-on data) gives an estimate of the individuals’ intervention adherence. Also, usage time will be assessed for every user who will upload the app at the end of the intervention.

#### Patient satisfaction

The Client Satisfaction Questionnaire [68, 69] has been optimized for the assessment of client satisfaction with internet interventions (Client Satisfaction Questionnaire adapted to Internet-based interventions [CSQ-I] [70]). We adapted this measure for the use of apps by replacing the word “training” with “app.” The CSQ-I is a valid and reliable (α between 0.93 and 0.95) measure of client satisfaction [70].

### Statistical analyses

The primary outcome of physical activity assessed with the respective subscale of the BSA-F at T4 (post-treatment of MoVo-App) will be analyzed as a dependent variable and its baseline value as a covariate, adjusted for sex and age and potentially other covariates. Continuous secondary outcomes will be analyzed accordingly. The statistical analysis for all research questions will be based on linear mixed-effects models with restricted maximum likelihood estimation to account for missing data [71]. The model is a mixture model, thus assuming two distinct distributions: (1) a binomial model (patients becoming physically active from inactivity and vice versa) and (2) a Gaussian distribution of minutes of physical activity per week for those being physically active. In the linear mixed-effects models, time (T1 to T5) will be the within-subjects factor, and intervention (MoVo-LISA and TAU plus MoVo-App vs. MoVo-LISA and TAU) will be the between-subjects factor. All two-way interactions will be considered. Main effects and interactions will be estimated for time points T3 to T5.

Baseline minutes of sport activity, age, sex, and body mass index will be included as covariates, along with other relevant demographic and clinical characteristics (e.g., disease, pain intensity, pain interference) collected through patient self-report. The model will allow for random intercepts, and all other factors will be treated as fixed effects. All statistical analyses will be performed using R software [72].

We expect to see a skewed distribution in our primary outcome physical activity, and, following guidance [72, 73], we will use transformations or consider using generalized or mixture-distribution mixed models [72]. Effects will be considered significant if *p* < 0.05. Assumptions for general, generalized, or mixture-distribution models will be checked graphically and with tests appropriate to the model [74, 75]. In addition, we will run several model checks by comparing increasingly complex models with different covariance structures, link functions, and estimation procedures with a null model via likelihood ratio tests and comparison of fit via the Akaike information criterion and Schwartz’s Bayesian information criterion [76].

To assess the mediating and moderating effects of psychosocial factors, the linear mixed-effects model of repeated measures will be extended by including psychosocial factors as random effect covariates. Their added effect as covariates, their interaction with IG, and a three-way interaction with IG and time will be estimated. It will be considered whether and how psychosocial intermediary effects depend on the intervention. Effects will be considered significant if *p* < 0.05.

The analysis does not consider a cluster effect of using two sites for the intervention. This decision is based on the high standardization in the delivery of the intervention and all study procedures in both sites. Differences in patient population between clinics will be accounted for by including demographic and clinical variables as covariates in the analysis. Furthermore, clinic was also used as a stratification factor in the randomization scheme (as detailed above).

Standardized mean differences and 95% confidence intervals will be calculated to measure the between-group effect size at post-treatment (T3) and follow-up (T4, T5). All analyses will be performed on an intention-to-treat basis. Completer (per-protocol) analyses will be conducted to investigate the influence of study attrition on study results. In addition, we will analyze the extent to which participants adhere to physical activity in accordance with the National Recommendations for Physical Activity and Physical Activity Promotion [77].

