**Methods/design:**

In this parallel-group randomized controlled trial, patients with musculoskeletal disorders will be randomized to either (a) a combination of the group-based intervention program MoVo-LISA to promote physical activity plus the MoVo-App or (b) the group-based intervention program alone without the app. The intervention group will receive the MoVo-App after discharge from inpatient rehabilitation. They receive help to increase and maintain their level of physical activity (initiated by the group program) by tracking their health goals, activity plans, major barriers, and barrier management that were developed during the group-based program. We will recruit 224 initially minimally active participants during orthopedic rehabilitation care. Outcomes are assessed at clinic admission; discharge; 6 weeks; and 3 (post-treatment), 6, and 12 months after discharge (follow-up). The primary outcome is sport activity (active/inactive and minutes of activity) at 6-month follow-up. Secondary outcomes are movement activity, cognitive mediators of behavioral change (e.g., self-efficacy, action planning), and health-related variables (e.g., pain intensity, depression). To evaluate intervention effects, linear mixed effects models (both on intention-to-treat basis with an additional per-protocol analysis) will be conducted with each outcome variable and with time as the within-subjects factor and group as the between-subjects factor, along with all two-way interactions and accounting for covariates as fixed effects.

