### Inclusion criteria

Patients are included if they fulfill the following inclusion criteria: (1) age 18 years or older; (2) musculoskeletal diagnosis classified in chapter M of the International Statistical Classification of Diseases and Related Health Problems, 10th Revision (ICD-10) [42], diagnosed by a physician; (3) sufficient knowledge of the German language; (4) ownership of a smartphone and internet access for online assessments; and (5) being physically inactive (sport activity < 30 min/week) in the last 3 months. Exclusion criteria are (1) rehabilitation following inpatient clinic treatment (e.g., due to surgery) and (2) not able to exercise for medical reasons. Eligible patients receive an invitation to participate in the study, an information letter/leaflet, and the informed consent form and complete the baseline online questionnaire (T0) during a study information meeting with a study assistant.

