### Primary outcome

The level of sport activity in minutes per week is measured with the BSA-F [51]. This is a validated German self-report instrument used to measure the level of movement activities (functional physical activities of daily living; *see* “Secondary outcomes” section below) and sport activities (sport- and health-related exercises, such as soccer, jogging, Nordic walking, Pilates, or fitness training) in minutes per week. For the sport activity subscale, the participants list a maximum of three sport activities in which they have engaged within the last 4 weeks. For each activity episode, participants indicate the frequency and duration in minutes. Activities that do not target larger groups of skeletal muscles and do not lead to maintenance of or increases in endurance, power, coordination, or flexibility are classified as invalid activities for this group. For each valid activity, an activity amount in minutes per week is calculated by multiplying frequency and duration divided by 4. All single amounts of the named sport activities are added to obtain the individual’s score on the Sport Activity Index. The validity of the BSA-F has been shown in several studies. However, data do not permit an analysis of the reliability of the instrument [51].

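### The minutes part of the two-part primary model compares only patients who are active at T4, so its group difference cannot be read as the app's effect on minutes

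*Protocol article*

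**What the plan says.** All references are to the protocol article.

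- **Abstract, Methods/design:** "The primary outcome is sport activity (active/inactive and minutes of activity) at 6-month follow-up". Both aspects are thus named as primary.
- **Primary outcome:** "The level of sport activity in minutes per week is measured with the BSA-F". The score is the sum over the valid activities a patient lists, so a patient with none scores 0.
- **Inclusion criteria:** patients must be "being physically inactive (sport activity < 30 min/week) in the last 3 months".
- **Statistical analyses, first paragraph:** T4 activity is the dependent variable and its baseline value a covariate. Then: "The model is a mixture model, thus assuming two distinct distributions". The first is binomial, for moving between inactivity and activity. The second is "a Gaussian distribution of minutes of physical activity per week for those being physically active".
- **Statistical analyses, later:** because skew is expected, "we will use transformations or consider using generalized or mixture-distribution mixed models". Standardised mean differences between groups are promised for T3, T4 and T5, and "All analyses will be performed on an intention-to-treat basis".
- **Proposed sample size/power calculations:** the effect is argued from average exercise duration (156 falling to 92 min/week) and expressed as standardised mean differences of 0.62 and 0.35. No share of active patients and no SD is given.

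The article does not say how the two parts combine into one effect on minutes, or which part decides if they disagree.

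**The concern.** Being active at T4 is acquired after randomisation and is itself half of the primary outcome. Study design lists starting activity and staying active (yes/no) among the things the app should support. If the app changes who is active, the active patients in the app arm include some who would have been inactive without it, and the control arm has no counterpart to them. The Gaussian coefficient then mixes a change in minutes with a change in who is counted. Adjusting for baseline minutes, age, sex and body mass index does not in general remove this, because the selection occurs after randomisation.

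At stake is the reading of one of the two stated primary results. An app that adds activity overall could show no difference, or a negative one, in the minutes part, and the plan does not say how to interpret that. The active-only difference is also not evidently the quantity behind the sample size, which is argued from mean minutes.

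**Working it through.** **Inputs from the protocol.** Mean of 92 min/week at 6 months with MoVo-LISA alone; 156 min/week directly after the intervention; d = 0.62 (main effect) and d = 0.35 (interaction); N = 224; 15% dropout; 1:1 allocation.

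**Derived.** If d = 0.62 standardises the fall from 156 to 92, the implied SD is (156 - 92)/0.62 = 64/0.62 = 103.2 min/week. The protocol does not state this SD.

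**The plan's own figure.** A two-sided 5% test with 80% power, d = 0.35 and covariate correlation 0.33 needs 2 x (1.96 + 0.84)² x (1 - 0.33²)/0.35², or 115 per arm. That is 230 before dropout and 230/0.85 = 271 after, so 224 is not reproduced. The article does not give its exact formula. This is a separate matter and nothing below depends on it.

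**Assumptions.** Inactive patients contribute 0 minutes. The app makes nobody inactive. pc and pt are the shares active in the control and app arms; mc = 92/pc is the mean among active controls; newly active patients do mi min/week; patients who would be active anyway gain g min/week.

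**Formulas.**
- Active-only difference = [(pt - pc)(mi - mc) + pc·g]/pt
- All-patient difference = (pt - pc)·mi + pc·g
- The active-only difference is zero at g = (pt - pc)(mc - mi)/pc

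**Main case: 60% v 70% active, mi = 60, g = 0.** mc = 92/0.6 = 153.3.
- Active-only: 0.1 x (60 - 153.3)/0.7 = -13.3 min/week
- All-patient: 0.1 x 60 = +6 min/week
- Break-even gain: 0.1 x 93.3/0.6 = 15.6 min/week

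**Other cases, mi = 60, g = 0.**

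| Active, control v app | Active-only difference | All-patient difference | Break-even g |
|---|---|---|---|
| 60% v 70% | -13.3 | +6 | 15.6 |
| 60% v 75% | -18.7 | +9 | 23.3 |
| 50% v 70% | -35.4 | +12 | 49.6 |

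**When the sign does not reverse.** At 60% v 70% with g = 20, the active-only difference is (-9.33 + 12)/0.7 = +3.8. Those active anyway gained 20, and the all-patient difference is 6 + 12 = +18. The component has the right sign but matches neither quantity.

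**Simulation.** 95 analysed per arm (224 x 0.85/2), 4,000 runs, gamma-distributed minutes, unadjusted comparison. The SD among the active is sqrt((103.2² - 0.24 x 153.3²)/0.6) = 91, and the newly active have SD 30.
- 60% v 70%: the active-only difference is negative in 78% of runs and significantly negative in 13%.
- 60% v 75%: negative in 88%, significantly negative in 21%.
- 60% v 60% with no effect: mean difference 0, with about 2% rejections in each tail. There is no bias when the app does not change who is active.

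**The case against.** Two-part models are a standard answer to an outcome with many zeros, and this one can be used properly: multiplying the two parts gives an all-patient mean. The plan also contains all-patient elements. The opening sentence on the T4 outcome has no restriction to active patients, standardised mean differences are promised, and the later wording on transformations leaves the model partly open. All of this stands. It means the deciding contrast is unsettled, not that the active-only contrast has been chosen to decide the trial.

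The illustration is also one-sided. The stated hypothesis is about maintaining activity that MoVo-LISA has started in both arms. If the app mainly adds minutes in patients who would be active anyway, the component can be positive. That stands too, and the break-even gains above show how strongly the sign depends on shares the protocol does not give.

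Three stronger readings are tempting but not supported:

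- **That the active-only part contradicts the intention-to-treat statement.** A two-part model uses every patient in the assigned arm: inactive patients inform the binomial part, active patients both. The problem is the interpretation of one coefficient, not the analysis set.
- **That the minutes part would lose a real effect.** If the whole of a 36 min/week benefit (0.35 x 103.2) came from raising the active share from 60% to about 84%, the minutes part would have about 5% power. But minutes among the active would not have changed, so a null there is correct, and the binomial part would detect the effect.
- **That sign reversal is to be expected.** It is possible under stated assumptions. Nothing in the protocol shows it to be likely.

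**Conclusion.** The point holds in limited form. The plan flatly specifies a minutes component restricted to patients active at follow-up and names minutes as part of the primary outcome. That difference does not compare groups formed by randomisation unless the app leaves activity status unchanged, and changing that status is one of the app's aims. The comparison of the share active is unaffected.

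The size cannot be fixed from the document. With control shares of 50% to 60%, app shares of 70% to 75%, newly active patients at 60 min/week and no gain in others, the active-only difference runs from -13 to -35 min/week while the all-patient difference runs from +6 to +12. The active shares, the newcomers' minutes and the zero gain are all assumptions. The later flexible wording does not cure the problem, because a transformed all-patient model and an active-only model answer different questions.

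**What to change.** In Statistical analyses, name the primary minutes effect as the difference between arms in mean sport minutes per week at T4 over all randomised patients, with inactive patients counted as 0. Obtain it in one of two ways:

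1. as the marginal mean difference from both parts of the two-part model, with a bootstrap or delta-method confidence interval; or
2. from the baseline-adjusted repeated-measures model on all minutes, with robust or bootstrap standard errors.

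Keep the share active at T4 as a randomised comparison. Report minutes among the active as description only, with no causal claim.

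The cost is a few sentences of wording and minor extra R code. The data needed are already collected.

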Can the combination of the face-to-face group-based intervention MoVo-LISA and MoVo-App increase maintenance of the initiated physical activity level in patients with musculoskeletal disorders more than MoVo-LISA without subsequent MoVo-App use?

We hypothesize that the additional MoVo-App can help to maintain the initiated level of physical activity (by the face-to-face group program) 6 months after clinic discharge in patients with musculoskeletal disorders more than MoVo-LISA without the app.

The following are secondary research questions:
2.Can the combination of MoVo-LISA and MoVo-App improve cognitive mediators of behavioral change (e.g., self-efficacy or action planning), and health-related variables (e.g., pain intensity, depression) in patients with musculoskeletal disorders more than the same face-to-face group-based intervention without subsequent MoVo-App use?3.Which cognitive and sociodemographic factors moderate and mediate the effects of MoVo-LISA and MoVo-App?

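### The single model planned for mediation and moderation yields no indirect effect, so its listed terms do not by themselves answer the mediation part of research question 3

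*Protocol article*

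**What the plan says.** Research question 3 (Background) asks: "Which cognitive and sociodemographic factors moderate and mediate the effects of MoVo-LISA and MoVo-App". The second part of Statistical analyses gives the method. "To assess the mediating and moderating effects of psychosocial factors, the linear mixed-effects model of repeated measures will be extended", and the sentence goes on to say how: the model is "extended by including psychosocial factors as random effect covariates". The quantities are then named: "Their added effect as covariates, their interaction with IG, and a three-way interaction with IG and time will be estimated". The interpretive aim follows: "It will be considered whether and how psychosocial intermediary effects depend on the intervention". The significance criterion is p < 0.05.

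Four other places bear on this:

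- The base model, described earlier in Statistical analyses: "The model will allow for random intercepts, and all other factors will be treated as fixed effects". Its time factor runs from T1 to T5.
- The Assessments section lists the cognitive variables among the secondary outcomes, and of these Statistical analyses says "Continuous secondary outcomes will be analyzed accordingly".
- Study design places T0 before randomisation and T1 to T5 at discharge or later.
- The sections on MoVo-LISA and on the control condition give MoVo-LISA to both arms. The arms differ only in the app.

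**The concern.** Mediation and moderation are different questions and need different data. Moderation asks whether the app's effect differs by a characteristic that the patient had before randomisation, and a factor-by-group interaction answers it. Mediation asks how much of the app's effect passes through a variable that the app changes. It needs the effect of group on the mediator, the effect of the mediator on a later outcome, and a quantity that joins the two.

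The article assigns both questions to one extension of the outcome model and lists only terms of that model. It is a stated method, not a gap left open. An analyst who follows it would have coefficients for every psychosocial factor and no estimate of mediation. The Discussion says that measuring these mediators will give a deeper understanding of how MoVo-LISA and the app work, so the result matters to what the trial intends to report.

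**Working it through.** The plan gives no figure on this point to reproduce. The check is structural, with a simulation as illustration.

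**1. What the listed terms measure.** Let G be group, M the factor and Y the outcome. Take M = a·G + other terms and Y = c·G + b·M + other terms. Then the indirect effect is a·b and the total effect is c + a·b. In the planned model:

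- the added effect of M estimates b;
- M by G estimates the difference in b between arms;
- M by G by time estimates how that difference changes over time.

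The path a appears in none of them. Shifting M by a constant within one arm leaves the slope of Y on M in that arm unchanged, so all three terms are the same whatever a is.

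**2. Simulation.** All parameters are assumptions in arbitrary units: 20,000 participants in two equal arms, three follow-up times, mean of five replicates.

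- M = a·G + 0.5·M0 + u·U + noise (SD 0.7)
- Y = c·G + b·M + u·U + person intercept (SD 0.6) + noise (SD 0.7)

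M0 is the baseline factor and U an unmeasured confounder, both standard normal. The fixed part, Y on G × M × time, was fitted by least squares.

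| Scenario | True a·b | M | G×M | G×M×time | G given M | Total effect | Path a |
|---|---|---|---|---|---|---|---|
| Full mediation: a 0.5, b 0.5, c 0, u 0 | 0.25 | 0.504 | -0.007 | -0.001 | 0.006 | 0.246 | 0.494 |
| No mediation: a 0, b 0.5, c 0, u 0 | 0 | 0.504 | -0.007 | -0.001 | 0.004 | -0.004 | -0.006 |
| No mediation, confounded: a 0.5, b 0, c 0.25, u 0.7 | 0 | 0.394 | -0.005 | -0.005 | 0.059 | 0.247 | 0.492 |

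Rows 1 and 2 agree on all three listed terms. They agree to the last digit because the same random draws were used and the terms do not depend on a. Only the total effect and path a separate them, and the mediation paragraph uses neither.

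Row 3 shows the opposite error. The factor has no effect on the outcome, yet its added effect is clearly non-zero. By arithmetic it should be u² / (0.5² + u² + 0.7²) = 0.49 / (0.25 + 0.49 + 0.49) = 0.49 / 1.23 = 0.398. A refit with a random intercept, as the base model has, left rows 1 and 2 equal to each other on the listed terms. It shrank the false association in row 3 without removing it, because the intercept absorbs part of a confounder that is constant over time.

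**3. Joining the paths.** A mediator model (M on G and time) with an outcome model (Y on G, M and time) gives a·b estimates of 0.247 and -0.003 in rows 1 and 2, against true values of 0.25 and 0. In row 3 it gives 0.492 × 0.394 = 0.194 against a true 0. The indirect effect therefore rests on there being no unmeasured mediator-outcome confounding.

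**4. Which measurement.** If T0 values enter the model, the factor cannot have been changed by the app and mediation cannot be assessed. If values from after randomisation enter, factor by group is not a clean moderation test, because the app may have altered the factor. No single choice serves both aims, and the paragraph states none.

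**5. Random or fixed.** An average added effect and interactions with group are fixed effects. A random slope describes how a coefficient varies between people. The random-effect label does not match the quantities listed in the next sentence.

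**The case against.** The strongest reply is that the components are already planned. The group effect on each cognitive variable is estimated as a secondary outcome (research question 2), and the factor-outcome association given group is the added effect. A reader might infer that the plan has neither path, and that would be wrong. What stands against the plan is narrower: no stated quantity joins the paths, and the mediation paragraph does not refer to the secondary-outcome analyses. A group-by-mediator term can also belong in a sound mediation model, so its presence is not itself an error.

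Three other strong readings are not supported:

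- That the plan mixes variables from before and after randomisation. The paragraph gives no measurement times, so using T0 for moderators and later values for mediators is compatible with it. The defect is that it does not say.
- That the random-effect wording contradicts the random-intercept sentence. That sentence describes the base model, and the later one says it extends that model. The wording is ill suited, but strictly it is no contradiction.
- That a full mediator would be declared significant in only 5% of trials. This assumes that mediation is judged on the interaction terms alone, a rule the article does not state. The added effect is also listed, and it was 0.504 under full mediation.

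It may also be said that such detail belongs in an analysis plan. That would answer silence, but the article names the model and the terms.

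**Conclusion.** The point holds in limited form. The listed terms do not by themselves identify mediation, and the plan names no indirect effect. It does not assign measurement times to the two aims, and its random-effect wording does not fit the average effects to be estimated. Research question 3 also asks about MoVo-LISA, which both arms receive, so mediation or moderation of its effect cannot be read from the randomised contrast.

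The size is qualitative. In the simulation the listed terms were identical for a true indirect effect of 0.25 and of 0. That equality follows from the algebra and does not depend on the assumed values. The confounded result (0.394 by least squares) does depend on them and only illustrates the direction of error.

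This concerns a secondary research question. The primary analysis of sport activity is unaffected. The change should be made, but it is not critical to the trial's main conclusion.

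**What to change.** Replace the mediation and moderation paragraph with two separate analyses.

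- **Moderation.** Enter the T0 value of each factor as a fixed effect and test factor by group.
- **Mediation.** Name the mediators and use a measurement taken after the app starts and before T4, that is T2 or T3. The Abstract puts T3 at 3 months and Study design at 4 months; either precedes T4 at 6 months. Adjust the mediator and outcome models for the T0 values of mediator and sport minutes. Report the indirect effect with a 95% CI, label it exploratory, and state the assumption of no unmeasured mediator-outcome confounding. If the two-part or a transformed outcome model is kept, state the scale of the indirect effect, since the simple product a·b applies to linear models.
- **Wording.** Replace the random-effect covariates with fixed effects.
- **Scope.** Limit mediation and moderation claims to the added MoVo-App.

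The cost is a rewritten paragraph and standard R code. No new assessment time is needed. The schedule figure is not shown in the text available, so confirm there that the chosen mediators are collected at T0 and at T2 or T3.
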